### Study procedure

Target patients will be screened for cognitive impairment by study staff at the time of hospital admission or shortly after when their clinical status allows for this. The screening procedure consists of assessments to estimate cognitive impairment (including delirium) and its severity, including the 4AT [49], the Richmond Agitation-Sedation Scale [50], and MMSE [29].

Those people meeting all the inclusion criteria will be informed personally and in writing about the intersec-CM trial. They will be invited to participate, and upon providing written informed consent, a baseline assessment will be conducted. The baseline assessment is based on the patients’ hospital records (sociodemographic data, ICD-10 diagnoses, and medication history) and a personal structured interview. The interview uses established and valid instruments to assess ADL (Barthel Index [51]), frailty (Edmonton Frailty Scale [33]), nutrition (screening items of the Mini Nutritional Assessment [52]), mobility (Hierarchical Assessment of Balance and Mobility [53]), pain (screening items), sleep quality (screening items from the Pittsburgh Sleep Quality Index [54]), and depression (screening items). The interview includes a comprehensive needs assessment based on the Camberwell Assessment of Need for the Elderly questionnaire [55] and an adapted version of the DelpHi-MV needs assessment [26, 40].

After the baseline assessment, each individual will be randomized using computerized permuted blocks into either the intervention or CAU group. This method ensures that the intervention and CAU participants are distributed evenly in a ratio of 1:1. Allocation to either the intervention or CAU is conducted at the study center after the baseline assessment so that the study staff are blind to the allocation during the initial assessment and cannot influence the allocation. Full blinding will not be possible once the intervention has started due to the type of intervention.

Immediately following randomization, standardized and systematic feedback based on clinically relevant parameters ascertained in the baseline assessment will be issued to the treating hospital staff (hospital information letter) in both groups. The letter includes assessment data. For the intervention group, it additionally includes recommendations for treatment and care for the discharge plan and for the preparation of ambulatory services, medication, social integration, and medical treatment after discharge. In both groups, the participant’s medical status at the time of discharge will be documented in their record. Patients in the intervention group will be contacted immediately after discharge, if possible in person, to continue the delivery of the intervention as outlined above. Otherwise, telephone contact is initiated with the intention to plan a timely in-person visit or visits by the specifically trained study nurses.

Follow-up assessments of all outcome measures for both groups will be conducted 3 months and 12 months after discharge in structured personal interviews, preferably at the participant’s home. The place and time of the follow-up assessments are chosen for the highest possible convenience of the participants.

### Data collection

Specially trained study staff will collect the data needed for the trial in computer-assisted face-to-face interviews and from patient records. All interviews will be standardized using validated and reliable questionnaires. To reduce interviewer bias, study staff will be retrained and supervised weekly to ensure the optimum degree of comparability. The source of information in the interviews will predominantly be the participant with cognitive impairment. However, due to the cognitive impairment, the validity of the information obtained may be compromised. The informal caregiver—if available—will validate facts (such as sociodemographic status and ADL) and fill in gaps in the patient’s answers. The source of each data item will be documented and controlled for.

Data will be stored on a tablet-based computer at the time of assessment. This allows for plausibility checks at the time of assessment and will avoid the errors that would otherwise result from transferring the data from written paper notes to a computer. Data collection will take place in the hospital (at screening and at baseline) and at the participants’ home (at the first and second follow-ups).

### Data analysis

#### Statistical analysis

The statistical analyses will be calculated on an *intention-to-treat* basis to reduce the impact of dropouts during the follow-up. These will include all individuals with baseline values of the outcome variables. Missing follow-up values will be imputed. To check whether systematic dropouts during the baseline assessment influenced the results, we will run multivariable logistic regressions with dropout as a dichotomous outcome (yes or no). The study group, sociodemographic variables, and clinical parameters assessed during screening (such as MMSE and the 4A test) will be included as predictors. These analyses will be performed for (1) all dropouts, (2) dropouts due to death, and (3) dropouts due to withdrawal of informed consent. To describe the study sample, appropriate summary statistics such as the mean, median, minimum, and maximum for continuous variables and frequencies and percentages for categorical data will be used.

The primary analyses will use separate generalized linear models to test intervention efficacy. The main outcome variables at follow-up 1 (3 months after discharge) and follow-up 2 (12 months after discharge) will be the dependent variables. The model specification will correspond to the scale level of the outcome variable under investigation. B-ADL will be assessed with a linear mixed regression, while for readmissions into hospital and institutionalization, logistic models will be used. The models will be adjusted for age, sex, and living situation of the patients. The study group is the predictor of interest (CAU vs. intervention). To account for the stochastic dependency of patients treated in the different hospitals (Bielefeld and Greifswald), study center will be included as a random effect variable. The baseline value of the outcome variable will be included as a covariate to reduce residual variance and to account for inter-individual variance at baseline. A positive intervention effect is defined as a significant regression coefficient (one-sided test) of the study group variable. Missing data will be imputed by multiple imputations via chained equations, stratified by study group. The overall alpha of the different primary outcome analyses will be adjusted using the Bonferroni–Holm procedure [56].

For the secondary analyses, sociodemographic variables (age under 80 or above 80), sex (man or woman), living situation (alone or not alone), and clinical parameters such as cognitive status, delirium, and frailty will be included. These variables either showed an impact in the DelpHi-MV study [24, 57] or are expected to moderate the health trajectory of elderly people in general. The inclusion of sociodemographic and clinical parameters should result in decreased residual variance and enhanced statistical power. To improve the quality of the regression models, possible interaction effects will be analyzed for study group, age group, living situation, and clinical parameters.

Economic evaluations will be conducted using methods that are consistent with those of published methodological guidelines for economic evaluations [58]. Health-care costs per patient will be calculated for a retrospective period of 3 months (follow-up 1) and 1 year (follow-up 2) from a public payers and societal perspective using published unit costs [59]. To analyze differences in quality-adjusted life years (QALYs) and costs, a linear mixed regression model will be used. The incremental cost-effectiveness ratio will be calculated using the incremental cost per QALY gained by the intervention compared with usual care. We will calculate the probability of the intervention being cost-effective at a wide range of willingness-to-pay margins using nonparametric bootstrapping to handle the sample uncertainty [60–62].

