PCI receiving intersectoral care management during the transition from hospital to their homes and into primary care will have better patient-oriented health outcomes than PCI receiving care as usual (CAU) at 3 and 12 months after discharge.PCI receiving intersectoral care management during the transition from hospital to home will have a lower frequency of unscheduled readmissions to hospital than PCI receiving CAU.PCI receiving intersectoral care management during the transition from hospital to home are less likely to be institutionalized 12 months after discharge from hospital than PCI receiving CAU.

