### Sample size

The estimated enrollment for the study is *n* = 398 participants plus their respective informal caregivers (where available). This sample size is necessary in the context of a complex intervention, which could not be proven to be efficacious in a smaller cohort. A sample size of *n* = 199 persons per arm is needed to detect effects on ADL with a Cohen’s *d* = 0.25 [47]. We expect Cohen’s *d* = 0.25 based on the DelpHi-MV study [24], which was approximately the size of the effect of the intervention on patients’ ADL (from preliminary analyses, since ADL were not the primary outcome in this trial, but a secondary outcome). As the Intersec-CM intervention is adapted from dementia care management, this should give a good estimate of what effect will be obtained. In a comparison between the intervention and control groups at a significance level of *p* = 0.05 and a statistical power of 80%, the sample size needed to obtain the same effect size as in the DelpHi-MV study (*d* = 0.25) is *n* = 199 patients per arm. This calculation includes that outcomes expected to deliver stronger effects are sufficiently powered.

Because of the longitudinal design, the sample size will decrease over time for various reasons. Loss to follow-up due to death, migration, withdrawal of informed consent, and nonparticipation for logistical and organizational reasons will occur. Migration is unlikely to have a large effect because the 70+ year-old group tends to be geographically stable. If a participant is lost to follow-up, efforts will be made to locate and recontact them. Data on those lost to follow-up will be included in the main analysis. Withdrawal of initial consent will be documented wherever possible together with the reasons provided. We expect that loss to follow-up will be approximately 30%, so that we expect at least *n* = 279 participants will provide a completed data assessment at the second follow-up visit.

In summary, the sample size is sufficient to detect even moderate effects on the outcomes. International studies are not readily comparable to the specificities of the German health-care system, and since this is the first randomized controlled trial addressing these research questions in Germany [48], we cannot precisely calculate our sample size based on previous studies and do rely to some extent on assumptions. The trial will aim to reach the sample size calculated and will be prolonged if recruitment takes longer than expected.

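### The stated 80% power is for one unadjusted one-sided ADL test at 0.05, but the plan tests ADL within a Bonferroni–Holm family of unstated size

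*Protocol article*

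**What the plan says.** The Sample size section rests on one outcome and one comparison. It gives 199 "persons per arm is needed to detect effects on ADL with a Cohen’s *d* = 0.25", and describes a two-group comparison "at a significance level of *p* = 0.05 and a statistical power of 80" per cent. It mentions neither a multiplicity adjustment nor whether the test is one- or two-sided. It adds that outcomes with larger expected effects are covered by the same calculation, but gives no rate or effect size for readmission or institutionalization.

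The Outcomes section names three primary outcomes: ADL (measured by the B-ADL), unscheduled readmissions and institutionalization. The Statistical analysis section plans separate models and states: "The main outcome variables at follow-up 1 (3 months after discharge) and follow-up 2 (12 months after discharge) will be the dependent variables". It fixes the direction of the test: "A positive intervention effect is defined as a significant regression coefficient (one-sided test) of the study group variable". On multiplicity it says: "The overall alpha of the different primary outcome analyses will be adjusted using the Bonferroni–Holm procedure". It does not give the number of tests.

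The hypotheses at the end of the Background section treat time differently for each outcome. The first, on patient-oriented health outcomes, names 3 and 12 months. The second, on readmissions, names no time. The third says that participants receiving the intervention "are less likely to be institutionalized 12 months after discharge from hospital than PCI receiving CAU".

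**The concern.** Holm's procedure gives a test the full 0.05 only after every other test in the family has been rejected. Otherwise ADL must meet a stricter level, starting at 0.05 divided by the number of tests. A sample size computed at 0.05 makes no allowance for this, so the stated power and the planned test do not match.

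Two things are at stake. The first is the stated chance of success on the one outcome the trial was sized for. The second is clarity about the primary test set: a reader cannot tell whether there are three tests, six, or another number, and both the first-step level and the power depend on it.

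**Working it through.** **Inputs.** From the Sample size section: d = 0.25, level 0.05, power 80%, 199 per arm. From the Statistical analysis section: one-sided testing, Bonferroni–Holm, two follow-up times. From the Outcomes section: three primary outcomes. From the Study procedure section: 1:1 allocation.

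**Method.** Two-sample t-test with n per arm, 2n − 2 degrees of freedom and noncentrality d·√(n/2). Power is the probability that this noncentral t exceeds the one-sided critical value at level α.

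**Step 1: reproduce the plan's figure.**
- Noncentrality: 0.25 × √(199/2) = 2.494.
- One-sided, α = 0.05: the smallest n giving 80% power is 199 per arm (power 80.1%). The normal approximation gives 198.
- Two-sided, α = 0.05: 253 per arm (normal approximation 252).

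So 199 corresponds to one one-sided test at the full 0.05, with no allowance for multiplicity.

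**Step 2: power at the first Holm step, d = 0.25, 199 per arm all analysed.**

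| Level for ADL | When it applies | Power | n per arm for 80% |
|---|---|---|---|
| 0.05 | all other primary tests already rejected | 80% | 199 |
| 0.05/2 = 0.025 | one other test still open | 70% | 253 |
| 0.05/3 = 0.0167 | first step, three tests | 64% | 284 |
| 0.05/6 = 0.0083 | first step, six tests | 54% | 337 |

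**Step 3: the complete three-test procedure.** The first step is the floor, because rejecting another outcome relaxes the level for ADL. This was simulated with three one-sided tests, 199 per arm, d = 0.25 for ADL and between-outcome correlation 0 to 0.3. The single-test power of the other two outcomes at 0.05 is an assumption, since the article gives no rates.

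| Assumed power of each other outcome | ADL power under Holm |
|---|---|
| no effect | about 64% |
| 50% | 68–69% |
| 80% | 73–74% |
| 90% | 76–77% |
| 95% | 78% |

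The shortfall against 80% is therefore about 2 to 16 percentage points.

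**Step 4: effect detectable with 80% power at the first step, 199 per arm.** Solving the Step 2 power formula for d gives about 0.30 for three tests and 0.33 for six, against the planned 0.25.

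**Step 5: the size of the family.** Read by outcome, Holm covers three tests. Read as the main outcomes at each follow-up, it covers 3 × 2 = 6. One linear mixed model for B-ADL might also cover both visits. The hypotheses give ADL two times (if it counts among the health outcomes), institutionalization one, and readmission none. No single count fits all the text, but the mismatch with the sample size is present for either three tests or six.

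**The case against.** **Holm is stepwise.** The 64% and 54% are worst cases, and the Sample size section expects stronger effects on other outcomes. This stands as a limit on the size of the problem: with strong other outcomes the three-test loss could be as small as about 2 points. It does not remove the problem. No rates are given to place the trial within the range, and 80% is reached only when all other rejections are certain.

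**Baseline adjustment could recover the loss.** Taking d = 0.25 as unadjusted, the correlation needed is √(1 − 199/284) ≈ 0.55 for three tests and √(1 − 199/337) ≈ 0.64 for six, with all 398 analysed. That is possible, but the article states no correlation and claims no such gain.

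**Listing the family belongs in the analysis plan.** Fair for the list itself. But the article fixes the sample size, level, power, sidedness and Holm, and a later document cannot make its 80% apply to the adjusted test.

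**The hypotheses need not define the family.** Also fair. The first agrees with the analysis, and the second is silent rather than contradictory. Only institutionalization clearly differs.

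Three stronger readings are tempting and not supported:
- A reader might infer that the family-wise error is not controlled. That would require splitting alpha by outcome and allowing success at either visit, a rule the article does not state. Read plainly, all primary analyses share one Holm family, which controls the error.
- A reader might add the expected 30% loss to follow-up and blame multiplicity for the total. Attrition is a separate matter: with 279 completers, power is already 67% at an unadjusted 0.05, and the plan is to impute missing values.
- A reader might conclude that 12 months must be the only primary time point. The first hypothesis names 3 months as well.

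**Conclusion.** The point holds. The arithmetic behind 199 per arm is correct for the comparison it describes, but that is not the comparison the analysis section plans. For the Holm-adjusted ADL test with 199 per arm analysed, first-step power is 64% (three tests) or 54% (six). Under full three-test Holm it is about 64% to 78%. These figures assume d = 0.25, one-sided testing as stated, no gain from covariates and no loss to follow-up; the upper end also assumes 95% power for each of the other outcomes. The size of the family cannot be settled from the text, and the one clear conflict is institutionalization: 12 months in the hypothesis, both follow-ups in the analysis.

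**What to change.** In the Statistical analysis section, list the outcome-by-time tests that form the Holm family and state how many there are. Reconcile the list with the hypotheses: settle institutionalization at 12 months or at both follow-ups, and give readmission a time.

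In the Sample size section, say that the calculation is one-sided and restate ADL power with 199 per arm at the first-step level: 64% for three tests or 54% for six. Alternatively, state the effect detectable with 80% power: d about 0.30 or 0.33. If credit is taken for stronger effects on the other outcomes or for baseline adjustment, state the rates or the correlation relied on.

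The cost is a less favourable stated power. No extra enrolment and no particular choice of time point is required.

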### Study population and selection criteria

Elderly PCI admitted to a general hospital with somatic illnesses are eligible for the study. The inclusion criteria for these index participants were as follows: age 70+ with cognitive impairment detected with a standardized screening instrument (Mini Mental State Examination, MMSE ≤ 26) [29], having lived at home prior to the index admission, living in the catchment area of the hospital, and providing written informed consent (personally or by their legal guardian when necessary). The exclusion criteria are acute stroke as the primary reason for admission, terminal disease, or insufficient language skills.

Since the treatment and care of elderly PCI may be dependent on informal caregivers, index participants are asked to name their informal caregivers (e.g., a spouse, child, or friend). The informal caregiver is then invited as an independent study participant upon provision of written informed consent. While we put effort into recruiting this group, the participation of an informal caregiver is not a necessary requirement for the inclusion of the index participant.

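### The secondary models split age at 80 where age in years would serve better, mainly at the expense of the exploratory study group by age interaction

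*Protocol article*

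**What the plan says.** The protocol article treats age in two ways within its Statistical analysis section.

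- **Primary models:** "The models will be adjusted for age, sex, and living situation of the patients". No categories are given for age.
- **Secondary analyses:** age is coded as "age under 80 or above 80". In full, the covariates are "sociodemographic variables (age under 80 or above 80), sex (man or woman), living situation (alone or not alone") together with clinical parameters such as cognitive status, delirium and frailty.
- **Reason given for the covariates:** they mattered in the earlier DelpHi-MV trial or are expected to moderate health trajectories in older people. Including them "should result in decreased residual variance and enhanced statistical power".
- **Interactions:** "possible interaction effects will be analyzed for study group, age group, living situation, and clinical parameters".

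Eligibility (Study population and selection criteria) is "age 70+ with cognitive impairment detected with a standardized screening instrument", so people aged exactly 80 can enter. The article reports no expected mean, spread or shape for age, no expected age effect, and no power for any interaction.

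**The concern.** Cutting a continuous covariate at one point treats patients aged 70 and 79 as alike and those just either side of 80 as different. When the relation with age is roughly linear, this loses information compared with age in years. The article gives reasons for including age but none for cutting it at 80.

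At stake is the study group by age interaction. The trial is sized for a main effect, so power for interactions is likely to be limited anyway, and grouping age lowers it further. It also forces any moderation by age into a step at 80. Separately, the two categories as worded leave age exactly 80 unassigned.

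**Working it through.** **1. The plan's own figure.** The Sample size section gives 199 per arm for d = 0.25, alpha 0.05 and 80% power. With a one-sided test, n = 2(1.645 + 0.842)²/0.25² = 197.8, so 198; the t-test version gives 198.5, so 199. The two-sided version gives 252. The figure therefore reproduces as one-sided, in line with the one-sided primary test. It does not depend on how age is coded and serves below only as a base for the adjustment check.

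**2. Information kept by the split.** For a linear age effect, the share kept is the squared correlation r² between age and the indicator age ≥ 80. For a normal variable cut at its median, r² = 2/π = 0.637, a loss of 36%. The article gives no age distribution, so the other rows are assumptions: normal ages truncated at 70 and at 103 (simulated), or uniform ages.

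| Assumed ages | Resulting mean | r² kept | Loss |
|---|---|---|---|
| Uniform 70-90 | 80 | 0.75 | 25% |
| Uniform 70-95 | 82.5 | 0.72 | 28% |
| Normal (78, SD 6) | 79.1 | 0.667 | 33% |
| Normal (80, SD 6) | 80.6 | 0.652 | 35% |
| Normal (82, SD 6) | 82.3 | 0.606 | 39% |
| Normal (84, SD 6) | 84.1 | 0.531 | 47% |
| Normal (85, SD 6) | 85.1 | 0.485 | 51% |

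The loss runs from about 25% to 50%. It grows as the cut at 80 moves away from the middle of the sample.

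**3. Effect on the interaction.** Take a linear study group by age interaction with 80% power on continuous age (two-sided 0.05). Its noncentrality is 1.960 + 0.842 = 2.802. After the split, power = Φ(2.802·√r² − 1.960), and the sample needed to recover the loss is multiplied by 1/r².

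- r² = 0.75: Φ(2.426 − 1.960) = 68%; factor 1.33
- r² = 0.637: Φ(2.236 − 1.960) = 61%; factor 1.57
- r² = 0.53: Φ(2.040 − 1.960) = 53%; factor 1.89
- r² = 0.485, the extreme row: Φ(1.951 − 1.960) = 50%; factor 2.06

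The 80% starting point is a reference for comparison. The article claims no such power.

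**4. Effect on adjustment of the treatment effect.** Take 199 per arm, d = 0.25, one-sided 0.05, and let age explain a share R² of outcome variance (assumed). Power = Φ(0.25·√(199/2)/√(1 − R²·k) − 1.645), where k = 0 without age, r² with the split and 1 with age in years.

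| R² | No age | Split, r² = 0.65 | Split, r² = 0.60 | Age in years |
|---|---|---|---|---|
| 0.02 | 80.2% | 80.7% | 80.6% | 80.9% |
| 0.05 | 80.2% | 81.3% | 81.3% | 82.0% |
| 0.10 | 80.2% | 82.5% | 82.3% | 83.7% |

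Before rounding, split versus years costs 0.2 to 1.4 points. Even at r² = 0.485 and R² = 0.10 it is 83.7 − 81.9 = 1.8 points.

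**5. People aged exactly 80.** If age is held in completed years, the truncated-normal distributions tried (means 75-85, SD 5-7 before truncation) put about 5-8% of participants at 80, that is 20-32 of 398. If age is computed to the day, almost nobody is exactly 80 and the gap disappears in practice.

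**The case against.** The strongest reply is that little depends on this, and most of that reply stands.

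- **Contradiction with the power statement.** A reader might infer that the article contradicts itself by promising power and then discarding it. It does not. The sentence "The inclusion of sociodemographic and clinical parameters should result in decreased residual variance and enhanced statistical power" compares including the covariates with leaving them out. Step 4 shows that a split age still helps relative to none.
- **A third of the information lost for adjustment.** A reader might carry the variance loss over to the treatment comparison. The cost there is at most one or two power points.
- **The size is assumed.** The article gives only a lower age limit, so no single percentage follows from it. Linearity is also assumed. If moderation really were a step at 80, the grouped term would be the better one.
- **The interaction is exploratory.** The main hypotheses do not mention age. The Outcomes section names frailty, delirium and service use as assumed moderators, and age enters only through the secondary models, where interactions serve to improve model quality. The cut is fixed in advance, which removes the worry of a cut chosen from the data.
- **Age 80.** A reader might infer that these patients would be dropped. Nothing says so; this is probably loose wording, and the boundary could be settled in an analysis plan that is not shown.

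What this does not answer is the choice itself. The two-group coding is stated, not left open, no reason is given for it, and the primary models name age without categories.

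**Conclusion.** The point holds as a minor one, confined to the exploratory secondary analyses. Coding age as two groups cut at 80 gives up information for the study group by age interaction. The loss is about 36% for a median split of a normal variable and about 25-50% over the distributions tried. An interaction with 80% power on continuous age would fall to about 61%, or 53-68% for losses of 47-25%. These figures rest on a linear age effect and on age distributions that the article does not supply.

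The documents do not support the inference that the trial's conclusions are at risk. The primary models, the Bonferroni-Holm adjustment and the 199 per arm do not depend on the split.

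**What to change.** In the secondary models, enter age in years, linearly or with a simple curve, and test study group by continuous age. If age groups are wanted for presentation, define them as under 80 and 80 or older, so that everyone has a place.

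The cost is a change of wording. No new data should be needed: the age criterion requires each patient's age to be known, and the baseline assessment takes sociodemographic data from hospital records. A curve uses one or two further model parameters. The change should be fixed before outcome data are examined by arm.

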### Intervention

The framework for the intervention is evidence-based dementia care management as conducted in the DelpHi-MV study [23, 24]. In principle, it consists of (i) a comprehensive assessment of the health and social status of the patient at the time of their admission to the hospital, (ii) a comprehensive needs assessment at the time of their admission to the hospital or shortly after, (iii) if applicable and available, an assessment of their informal caregiver’s health and burden, (iv) systematic written feedback to the treating hospital physician and nursing staff with recommendations for treatment and care for the patient after discharge (hospital information letter; these recommendations are based on predefined algorithms using the results of the assessment), (v) an assessment of the patient’s health at the time of discharge, (vi) a comprehensive needs assessment at the patient’s home immediately after discharge, (vii) if applicable and available, an assessment of the informal caregiver’s health and burden at the patient´s home, and (viii) support in meeting the patient’s needs as identified by the assessment.

The entire intervention delivery by specifically trained study nurses (case manager, social worker, or dementia care manager) [30] will be supported by a computerized tablet-based intervention management system for intersectoral care management. The system is a rule-based expert decision support system that matches individual patient characteristics to recommendations for treatment and care. The system supports the identification of a patient’s unmet needs, selects corresponding patient-specific interventions, and integrates these into an individualized intervention plan. The intervention management system has been proven to support the systematic identification of unmet needs, to improve the selection of specific intervention modules, and to address them systematically [25, 28].

The intervention used in this study does not, however, replace any provisions offered by other providers in the hospital or in ambulatory settings.

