**Fig. 2 Fig2:**
[figure not shown]
Schedule of enrollment, intervention, and assessments in accordance with the Standard Protocol Items: Recommendations for Interventional Trials (SPIRIT) guidelines. SCR screening at the time of admission to hospital, BL baseline after having provided written informed consent, *I*_1_ during hospital stay, *I*_2_ day of discharge, *I*_3_ up to 3 days after hospital discharge, *I*_4_ period up to 3 months after discharge, *FU*_1_ 3 months after discharge, *FU*_2_ 12 months after discharge

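### Both cost look-back windows open at discharge, so health-care costs between in-hospital randomization and discharge fall outside the incremental cost as written

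*Protocol article*

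**What the plan says.** The economic part of the Statistical analysis section fixes the cost windows: "Health-care costs per patient will be calculated for a retrospective period of 3 months (follow-up 1) and 1 year (follow-up 2". These costs feed a linear mixed model, an incremental cost-effectiveness ratio and a bootstrap probability of cost-effectiveness. The viewpoint is that of payers and of society.

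Study procedure fixes the visits: "Follow-up assessments of all outcome measures for both groups will be conducted 3 months and 12 months after discharge". The Fig. 2 legend gives the same timing.

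Randomization comes before discharge. Study procedure says: "After the baseline assessment, each individual will be randomized using computerized permuted blocks into either the intervention or CAU group". The Data collection section places the baseline assessment in the hospital: "Data collection will take place in the hospital (at screening and at baseline".

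The arms are treated differently from that moment. Both receive a hospital information letter straight after randomization, but according to Study procedure: "For the intervention group, it additionally includes recommendations for treatment and care for the discharge plan and for the preparation of ambulatory services". The Fig. 2 legend lists intervention points during the stay (I1) and on the day of discharge (I2). The Intervention section names, as one component, "an assessment of the patient’s health at the time of discharge".

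No section adds the remaining index stay to the costs, and none says when QALY accrual begins.

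**The concern.** An incremental cost compares what follows from being assigned to one arm with what follows from being assigned to the other, so its clock should start at assignment. Here assignment happens in hospital, while the cost clock is set by visits counted from discharge. The uncovered interval is the one in which the intervention first acts, and it acts on discharge planning. If the added recommendations lengthen or shorten the remaining stay, those bed-days are a cost difference between the arms that the stated windows do not capture.

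What is at stake is the incremental cost, and through it the cost-effectiveness ratio and the probability of cost-effectiveness. The Discussion presents the cost-effectiveness analyses as support for moving the intervention into routine care, so an incomplete incremental cost matters for that use.

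**Working it through.** The article gives no cost, QALY or length-of-stay figure to reproduce. The check therefore concerns timing.

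**Inputs.** Look-back of 3 months at follow-up 1 and 12 months at follow-up 2 (Statistical analysis). Visits at 3 and 12 months after discharge (Study procedure, Fig. 2 legend). Randomization after an in-hospital baseline (Study procedure, Data collection).

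**1. Where the windows open.** Window start relative to discharge = visit time − look-back length.
- Follow-up 1: 3 − 3 = 0 months.
- Follow-up 2: 12 − 12 = 0 months.

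Both open at discharge. Randomization lies before that point, so neither window covers the interval from randomization to discharge.

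**2. Visits off schedule.** If a visit is *d* days late, its window opens *d* days after discharge and misses the first *d* days at home as well. If it is *d* days early, the window reaches *d* days back towards the stay. Coverage of the interval then depends on visit scheduling rather than on a rule.

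**3. How much time is uncovered.** Share of the period from randomization to follow-up 2 = L / (365 + L), where L is the number of inpatient days after randomization. The article does not give L, so these values are assumptions:
- L = 3: 3/368 = 0.8%
- L = 7: 7/372 = 1.9%
- L = 14: 14/379 = 3.7%
- L = 30: 30/395 = 7.6%

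These are shares of time, not of cost. All of the time is inpatient.

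**4. What this does to the incremental cost.** The missing term is the mean cost from randomization to discharge in the intervention arm minus the same mean under usual care. It is zero if the arms do not differ in that interval, and otherwise takes the sign of the difference. Nothing in the article fixes its size or sign.

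**5. How the two windows relate.** Follow-up 1 covers months 0–3 and follow-up 2 covers months 0–12. Their sum would represent 3 + 12 = 15 months of cost for 12 calendar months. This matters only if they are added.

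**6. A figure that does not help.** The Study design section allows 13 months from last enrolment (31 October 2019) to last follow-up (30 November 2020). That is 396 days, or 396 − 365 = 31 days beyond one year. The excess may include any scheduling allowance, so it does not estimate the uncovered stay.

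**The case against.** The strongest reply is that this is one condensed paragraph, which refers to published guidelines for economic evaluation, and that the full protocol may cost the index stay and the delivery of the intervention separately. For delivery cost this stands. A reader might infer that care-manager time in hospital is left out, but the windows are stated for health-care costs per patient, and nothing confines delivery cost to them. For the remaining index stay the reply is weaker: it is health care, the windows for health care are stated explicitly, and followed as written they leave it out.

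A second reply is that little differs by arm before discharge. The needs assessment precedes randomization in everyone, both arms get a letter with assessment data, and discharge status is documented in both. No section hypothesizes an effect on length of stay. This limits the likely size but does not remove the possibility, because the added recommendations concern the discharge plan itself and intervention points are scheduled in the stay.

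A third reply is that the service-use questionnaire asks about hospital admissions over 12 months, which at follow-up 1 reaches back before discharge. That item is described as a count of admissions, and the cost window stated for that visit is 3 months, so it does not supply post-randomization days.

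A reader might also infer that months 0–3 are counted twice in the mixed model. The text does not say that the two costs are summed or stacked. Two separate horizons, each with its own cumulative cost, is an equally natural reading.

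**Conclusion.** The point holds for health-care costs on the stated rule. At nominal visit times both windows open at discharge, and costs between randomization and discharge are outside the incremental cost as written. It rests on three assumptions: visits occur on schedule, the windows are applied literally, and no document not shown here adds the stay.

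The uncovered time is 0.8% to 7.6% of the period for assumed stays of 3 to 30 days. The documents do not support a stronger statement that the cost-effectiveness ratio will be wrong, or wrong by some amount per QALY. They contain no cost or QALY figures, and the direction is open because the stay could lengthen or shorten.

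The gap is shown for costs only, since the start of QALY accrual is not stated. Cost-effectiveness is a planned supporting analysis, so no primary outcome is affected. The change should still be made, because it removes a possible bias at little cost.

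**What to change.** - Start cost accrual at randomization. In both arms, add index-stay days from randomization to discharge, taken from the hospital records the study already uses.
- State that the QALY horizon also starts at randomization.
- Count the cost of in-hospital intervention delivery from whatever staff-time records exist, or from a standard time per component. The Intervention section does not say that the computerized system logs staff time, and 236 participants had been enrolled by 22 July 2019, so actual times may not be recoverable for all.
- Define the total per patient as the 1-year window plus the post-randomization index stay. Do not add the 3-month cost, because months 0–3 already lie inside the 1-year window; report it, if wanted, as a separate horizon.

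The cost is slightly more data extraction, a revised economic paragraph and possibly a less favourable ratio. No extra patient visits are needed.
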